## Abstract

**Background:**

Neck pain is one of the most common work-related musculoskeletal disorders (WMSDs). It has important social and economic consequences such as reduced productivity due to absenteeism, leave, and early retirement and financial losses due to medical expenses for the workforce especially teachers. This study aims to evaluate whether a model-based social media intervention could change the high-risk behaviors that cause work-related neck pain among teachers.

**Methods:**

This is a randomized controlled trial that will be done in three steps. The first stage is a qualitative study to obtain the items and areas of the researcher-made questionnaire based on the health belief model (HBM), the second stage is the psychometric evaluation of the questionnaire, and the third stage is designing and implementation of model-based educational intervention in social media context. The study population is teachers who working in junior high school in the 19th district of education minister in Tehran, Iran, which are randomly divided into two groups of intervention and control. The intervention group receives training packages on social media, and the control group does not receive any training. The educational intervention tries to improve the knowledge, attitude, skills, and self-efficacy in adopting neck pain prevention behaviors among teachers. The study will also assess whether the intervention can promote preventive neck pain behavior among teachers.

**Discussion:**

Work-related neck pain can have a negative impact on teachers’ health. This study is an attempt to investigate the impact of developed interventions in promoting preventive behavior regarding work-related neck pain through social media context.

**Trial registration:**

Iranian registry of Clinical Trial (IRCT) IRCT20210301050542N1. Registered on 16 March 2021

Ethics code: IR.MODARES.REC.1399.163

## Background

Work-related musculoskeletal disorders (WMSDs) are one of the largest occupational health problems in the working population in developing and developed countries, with the highest number of occupational complaints with different severity [1, 2]. Furthermore, social and economic consequences for the workforces have been evident in many studies [3, 4]. Performing work tasks in inappropriate physical, psychological, and ergonomic conditions causes disorders in the bones, nerves, tendons, ligaments, muscles, and blood vessels and causes pain in the neck, back, shoulders, elbows, wrists, arms, and hands [5–7]. It has been estimated that about 44% of all occupational diseases are musculoskeletal disorders which caused by WMSDs [8].

Neck pain is one of the most common and costly health challenges in the workplace [9, 10] that affects about 52–58% of the population during life [8]. Neck pain (NP) has a significant impact on social functioning and health status which lead to inability to perform daily activities and consequently reduced quality of life as well as imposing health costs on society and governments [11, 12]. The prevalence of neck pain varies in different professions [1, 13]. Teachers have been shown to have a higher percentage of work-related musculoskeletal disorders than other occupations [1, 2, 6]; hereby, it has been argued that neck pain among teachers is the fourth their health problem [3, 14].

Neck pain in teachers is caused by several reasons such as age, gender, duration of employment, use of inappropriate body postures, uncontrolled stress, high workload, prolonged sitting and standing, and job dissatisfaction as well as doing monotonous and repetitive tasks [4, 15–17]. The consequences of neck pain on teachers’ life include frequent leave and absences from workplace, reduced individual and social functioning, early retirement, inability to perform activities, and the imposition of health costs [18].

It has been discussed that various factors such as demographic factors (body mass index, vitamin D deficiency), physical factors such as excessive computer use, prolonged sitting and standing, excessive bending of the trunk, squatting, bending over neck forward backward, keeping hands above shoulder level for a long time, doing strenuous activities and unprincipled exercise at work or outside, lack of adequate rest time during working hours and psychosocial factors such as work-related stress, lack of attention and support from colleagues, marital and family relationships, job dissatisfaction, weak interpersonal relationships, organizational characteristics, and financial–social aspects cause neck pain [19–21]. Many of these mentioned various factors is rooted in unhealthy and high-risk behaviors which done by individuals specially teachers [11, 12, 22, 23]. Reducing neck pain was possible if teachers could observe and maintain correct behaviors during their working and daily activities [7, 24]. It seems that the main obstacles in training teachers to do preventive neck pain behaviors are lack of time required for on-the-job training, lack of ergonomic equipment in the workplace, lack of adequate rest time at work, and health care costs [22].

Education through social media or participatory internet refers to a set of activities and communications that are done using electronic devices such as audio/video equipment, computer networks, and virtual tools on the Internet. In fact, all communication that is done through the internet and in the context of social networks and remotely without face-to-face interaction and leads to learning is called internet learning. In fact, this type of communication can provide a fraction of different information to a large number of users over long distances which is also economically viable [25, 26]. At present, the use of social networks has become as one of the best ways to promote health due to its effectiveness in reaching the general audience [27]. Moreover, due to the outbreak of the massive corona pandemic, it will be impossible to implement in- person educational intervention for teachers, so social interactive educational intervention is really recommended.

Different studies showed that model-based interventions are more effective to reducing musculoskeletal disorders compared with non-model ones [28, 29]. One of the best effective models that address lacked perception of people to promote preventive behaviors is the health belief model (HBM); its constructs were shown in Fig. 1 [28, 30, 31]. Numerous studies have shown that educational interventions based on health belief model is so effective on promoting preventive behaviors and behavior modification which could reduce musculoskeletal disorders such as low back pain and neck and shoulder pain [32–34].

**Fig. 1 Fig1:**
[figure not shown]
The constructs of health belief model

Accordingly, the first phase of this research project was done through interviews with the teachers based on this model, and the results clarified that they did not perceive the severity of neck pain consequences. Furthermore, they did not consider themselves as susceptible individuals for neck pain if they would not comply with preventive behaviors. On the other hand, they did not understand the benefits of neck pain preventive behaviors and so they mentioned many barriers including being unskilled to do these preventive behaviors. In other words, they lacked sufficient self-efficacy. Therefore, it was concluded that health belief model would be a proper model which possibly can overcome these causative factors of not doing preventive behaviors by teachers.

Therefore, according to address these limitations, this protocol aims to develop an intervention based on the health belief model in social media context in order to promote preventive behaviors among the school teachers.

*To achieve the overall goal, three following phases needed to be considered:*

Phase1: Carrying out a qualitative study to determine the leading factors influence doing neck pain preventive behaviors and domain/item generation of researcher-made questionnaire

Phase 2: Psychometrics of the developed questionnaire

Phase 3: Designing and implementation of an educational intervention based on the health belief model in the context of social networks to adopt behaviors that to reduce neck pain in teachers

## Methods/design

The design of this protocol is a randomized clinical trial. The final purpose is to develop and evaluate a model-based social media intervention regarding behavioral work-related neck pain among school teachers. To reach this aim, the following phases which are shown in Table 1 should be done.

**Table 1 Tab1:** The study overview

Phases and participants	Aim	Methods
Phase 1		
Qualitative study on teachers	Step 1: Identifying occupational factors that cause neck pain, impact of neck pain on daily life activities, neck pain preventive behaviors, and affective factors	In-depth interviews
Researcher	Step 2: Designing of an initial questionnaire	Based on step 1
Phase 2		
Psychometrics evaluation	To validate the questionnaire Preparation of the final questionnaire	By research team factor analysis, varimax questionnaire, rotation, content validity index, and impact score
Phase 3		
Design interventions researcher	Step 1: Intervention group training	Based on social media
Implementation teachers	Step 2: Transfer educational content to intervention group	Based on social media
Intervention evaluation teachers	Step 3: Evaluate the program Identify the impact of the program in the intervention group	Questionnaire checklist

The first phase of the research is a qualitative study that is done through interviewing with 25 teachers. Criteria for entering into this phase of the research are as follows: having a work-related neck pain experience and willingness and ability to share his/her experiences. Data collection will be done through semi-structured interview guild line with the participants. The questions are designed based on the health belief model. Participants are asked questions about their experiences about work-related neck pain, its consequences and effects on their work and life, the extent to which teachers suffer from neck pain, the behavioral factors that cause this problem, and the effective neck pain preventive behaviors as well as the benefits/barriers of doing the behaviors and how they are confident that they could do these behaviors. Based on the content analysis of the collected data from the interview, the main categories based on HBM and items of each domain of the researcher-made questionnaire are determined.

The second phase of this study is psychometry evaluation of the researcher-made questionnaire that is made in previous phase. In this phase, the researcher-made questionnaire is subject to content validity and face validity by 15 specialists in health education/health promotion, ergonomics, physiotherapy, and occupational health. Exploratory factor analysis and scale correlation matrix will also be used to evaluate the construct validity and to obtain the final items of the questionnaire in each domain.

The third phase of the study includes designing, implementing and evaluation of a model -based social media intervention for promoting preventive behaviors due to work-related neck pain (Fig. 2).

**Fig. 2 Fig2:**
[figure not shown]
Consort flow diagram

### Sampling

At this stage, a list of all 26 schools in district 19 of education ministry in Tehran will be prepared. From the schools, people are randomly selected and then randomly divided into two groups of intervention and control. The intervention group receives a training program while the control group does not receive any training program. Participants are evaluated in three time points of before the intervention, 1 and 3 months after the intervention. The study setting will be public schools in the 19th district of education ministry in Tehran city of Iran. The schools in this district are located in center of city that is almost similar to majority of other schools. Participants are teachers of junior high school.

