### Calculating sample size

Based on the similar existed evidence (21) and considering the 95% confidence level and 80% test power, the number of necessary samples for each group (intervention and control) according to Pocock formula is 63 people which plus 10% for dropout would be of 73 people in each group finally. For randomization, first, a list of teachers’ telephone numbers with a specific code is prepared, and the codes are poured into a bag and randomly divided into two groups of intervention and control. This study is a double-blind study, so the researcher and participants are not aware of about the grouping of individuals.

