#### Implementation of intervention

Participants can communicate with the researcher by email and phone call. The intervention group will receive training in the form of webinars, group discussions, questions and answers, videos, animations, posters, pamphlets, and infographics. The procedure of teacher training is supervised by the researcher. The training will be provided to the intervention group through social media for 1 month. After, the reminder training will be provided to the intervention group for 3 months. During this period, the control group will not receive any intervention. However, the training package will be provided to the control group after the study is finished. Although there is no auditing plan in this study, if there are any participants with this problem, he/she will be excluded from the study.

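### Teachers from the same 26 schools are individually randomised to copyable social-media material, and the article describes no step that limits or measures control-arm exposure, so a null result would be hard to interpret

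*Protocol article*

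**What the plan says.** **Unit of allocation.** The Sampling section starts from a frame of schools ("a list of all 26 schools in district 19 of education ministry in Tehran will be prepared") but then draws and allocates teachers: "From the schools, people are randomly selected and then randomly divided into two groups of intervention and control". Calculating sample size gives the mechanism: each teacher has a code, and "the codes are poured into a bag and randomly divided into two groups of intervention and control". School is neither the unit of allocation nor a stratum.

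**Treatment.** Under Implementation of intervention: "The intervention group will receive training in the form of webinars, group discussions, questions and answers, videos, animations, posters, pamphlets, and infographics". Delivery is through social media for 1 month, followed by 3 months of reminder training.

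**Control condition.** "During this period, the control group will not receive any intervention". Controls are given the package once the study is over.

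**Possible safeguard.** The same section ends by saying that no auditing is planned and that participants who have an unspecified problem will be excluded. The problem is not defined.

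**Power.** The sample size is 63 per group, raised to 73 for dropout, "considering the 95% confidence level and 80% test power". No effect size or standard deviation is given, only a citation, and no allowance for exposure of controls is mentioned. The limitations in the Discussion are self-report and short follow-up; contamination is not among them.

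**The concern.** Both arms come from one set of workplaces, and much of the treatment can be copied and sent on. A control teacher who receives the videos or posters from a colleague, or talks the content through with one, is partly treated. The main outcome is self-reported preventive behaviour, compared between arms by a t test, so partial treatment of controls shrinks the contrast being tested.

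Two things follow. Power falls below the stated level. More importantly, if exposure is not recorded, a result near zero has two explanations that the data cannot tell apart: the programme does not change behaviour, or it does and the controls had it too. The protocol says its data will show whether the education is effective, so this ambiguity falls on its central question. Exposure that is not asked about during follow-up cannot be recovered reliably later.

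**Working it through.** **Inputs from the article:** 26 schools; 63 per group, 73 after the dropout allowance; 10% dropout; 95% confidence; 80% power; equal groups.

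**Assumptions, not in the article:** a two-sided test; a standardised difference d, because no effect size is given; and a dilution c, the share of the true effect lost because controls are partly treated. As an illustration, c = 10% arises if 10% of controls take up the whole programme, or if 20% take up half of it.

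**1. The stated sample size.** For two means, n per group = 2(1.96 + 0.84)² / d². With d = 0.5 and unrounded normal quantiles this is 62.8, which rounds up to 63. So d = 0.5 fits the stated figure, but it is back-solved. The step from 63 to 73 is a separate matter (63/0.9 = 70) and does not affect this point.

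**2. Opportunity for contact.** Total recruited: 2 × 73 = 146. Per school: 146/26 = 5.6. If teachers are spread at random over the schools, a given control has no intervention colleague in the same school with probability (25/26)^73 = 0.057. About 94% of controls therefore have at least one; an equal spread over schools gives about 96%. This is the share with the opportunity for contact, not the share exposed.

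**3. Power under dilution.** The effect becomes d(1 − c) = 0.5(1 − c). The power of a two-sided 5% two-sample t test is shown for the 63 per arm of the calculation, and for 66 per arm, which is what remains of 73 after 10% dropout (73 × 0.9 = 65.7).

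| Effect lost (c) | Diluted d | Power, 63 per arm | Power, 66 per arm |
|---|---|---|---|
| 0% | 0.50 | 80% | 81% |
| 10% | 0.45 | 71% | 73% |
| 20% | 0.40 | 61% | 63% |
| 30% | 0.35 | 50% | 51% |

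**4. Size needed to hold 80% power.** The required n grows by 1/(1 − c)². At c = 10% this is 63/0.81 = 77.8, so 78 per group before dropout; at c = 20% it is 63/0.64 = 98.4, so 99.

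**5. Does any stated measure close the route?**

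- The double-blind statement does not limit sharing. Teachers who did not know their group would have no reason to withhold material from colleagues.
- The exclusion of participants with an undefined problem does not serve either. If it means exposed controls, no auditing is planned to find them, and removing them after randomisation would break the randomised comparison.

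**The case against.** The strongest reply is that most of this is silence in a condensed article. Platform settings, exact questionnaire items and supporting analyses are commonly left to a full protocol or analysis plan, and neither is shown. That stands as a limit on wording: the article describes no safeguard, which does not prove that none exists. The questionnaire section lists domains, and the final items depend on the earlier phases, so one cannot assert that no exposure item will be included. What the article does fix is individual allocation within shared schools, a copyable medium and controls taken as untreated.

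Other tempting readings also go too far:

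- A reader might take the 94% as the share of controls who will be contaminated. It counts only those with an intervention colleague.
- A reader might picture both arms together in staff rooms. The article does not say so, and its Background says in-person education was impossible because of the pandemic. Online contact between colleagues remains a route.
- A reader might suppose that a forwarded poster transfers the programme. Webinars, group discussions and questions and answers do not transfer that easily.
- A reader might conclude that schools should have been randomised. That is a genuine trade-off: with about 5.6 teachers per school, clustering has its own cost. At an assumed intraclass correlation of 0.05 the design effect is 1 + 4.6 × 0.05 = 1.23. The documents do not show that choice to be better.
- A reader might infer that a positive result would be suspect. Leakage biases towards no difference, so it would not.

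Remedies have costs too. Recording school on anonymous forms, with about 2.8 teachers per arm per school, could identify people. A no-sharing request made to one arm only would reveal allocation.

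**Conclusion.** The concern holds as a gap in what a null result could mean, not as evidence that contamination will occur. Individual allocation within 26 shared schools, material that can be passed on for about four months, and controls assumed to be unexposed are all in the text. The one sentence that might be a safeguard is undefined and unaudited, and would act after randomisation.

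The size is conditional. Assuming d = 0.5, losing a tenth of the effect takes power from about 80% to 71% at 63 per arm, or from about 81% to 73% at 66 per arm; losing a fifth takes it to 61% or 63%. The true dilution is unknown and may be small. That material can be forwarded, and that most schools will hold both arms, are inferences from the formats and the allocation method; the second is close to certain on the numbers. The plan should be changed because the remedy is cheap and must be in place before follow-up.

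**What to change.** Keep individual randomisation, and keep the comparison of teachers as randomised as primary. Then:

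1. Put one or two exposure items last in the 1- and 3-month questionnaires for both arms: whether the teacher has seen, been sent or discussed the trial material. Link forms to arm by code, without name or school. The planned paired comparisons already need forms linked over time.
2. Deliver the material in an invitation-only channel, and ask all participants, in neutral wording, not to pass study material on until the study ends. Addressing everyone avoids disclosing the arm.
3. Report control-arm exposure at each time point beside the primary result.
4. Replace the undefined exclusion with a statement that exposed participants stay in the as-randomised analysis.
5. State under Calculating sample size that 80% power assumes no leakage.

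A complier-average estimate is optional, and worthwhile only if receipt of the programme is defined in advance.

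**Cost.** One or two items, one request and a short table; no extra participants. The items may slightly prompt controls' curiosity, which is why they go last. Exposure will be self-reported and imprecise, and the power statement becomes less favourable.

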### Calculating sample size

Based on the similar existed evidence (21) and considering the 95% confidence level and 80% test power, the number of necessary samples for each group (intervention and control) according to Pocock formula is 63 people which plus 10% for dropout would be of 73 people in each group finally. For randomization, first, a list of teachers’ telephone numbers with a specific code is prepared, and the codes are poured into a bag and randomly divided into two groups of intervention and control. This study is a double-blind study, so the researcher and participants are not aware of about the grouping of individuals.

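### The stated sample size does not follow from its own inputs: 63 per group plus 10% for dropout is 70, not 73

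*Protocol article*

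**What the plan says.** The whole calculation stands in one sentence of the protocol article, under Calculating sample size. It rests on a cited earlier study ("Based on the similar existed evidence (21") and on error rates given by "considering the 95% confidence level and 80% test power". The sentence presents its base number as "the number of necessary samples for each group (intervention and control". It then gives the base, the allowance and the total in one run: the number required "is 63 people which plus 10% for dropout would be of 73 people in each group finally".

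The text shown gives no other sample size, dropout rate or rounding rule. The CONSORT flow diagram (Fig. 2) is not reproduced in the text available for review.

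**The concern.** A base number, a dropout rate and an inflated number are tied together by simple arithmetic: any two fix the third, up to rounding. Here all three are stated and they do not fit, so at least one is wrong.

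What is at stake is the clarity of the recruitment target and of the loss to follow-up that the design tolerates. Outcomes are collected up to 3 months after the intervention, so readers will compare the loss observed with the loss allowed for. The sentence supports two answers. Its wording says 10%, while its own pair of numbers, 63 and 73, implies about 14%.

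**Working it through.** **Inputs**, all from Calculating sample size: base n = 63 per group; dropout d = 10%; final N = 73 per group; two groups of equal size.

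**Step 1. Try to reproduce 73 from 63 and 10%.**

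- Division, N = n/(1 - d): 63/0.90 = 70.0, so 70.
- Multiplication, N = n x (1 + d): 63 x 1.10 = 69.3, rounded up to 70.
- Inflating the total of 2 x 63 = 126: 126/0.90 = 140, or 126 x 1.10 = 138.6. Both give 70 per group once rounded up to equal groups.
- Applying the 10% twice: 63 x 1.10 x 1.10 = 76.2, or 63/0.90/0.90 = 77.8. These overshoot 73.

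None of these gives 73. The gap to the usual answer is 73 - 70 = 3 per group, or 146 - 140 = 6 in total (6/140 = 4.3%).

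**Step 2. Ask what would give 73.**

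| Figures kept | Figure that must change | Arithmetic |
|---|---|---|
| 63 and 10% | final number becomes 70 | 63/0.90 = 70.0; 63 x 1.10 = 69.3 |
| 63 and 73 | allowance becomes about 13.7% loss (or a 15.9% addition) | 1 - 63/73 = 0.137; 73/63 - 1 = 0.159 |
| 10% and 73 | base becomes 65 (division) or 66 (multiplication) | 65/0.90 = 72.2, rounded up to 73; 66 x 1.10 = 72.6, rounded up to 73 |

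In addition, 63 + 10 = 73. Ten people may have been added where 10% was meant, but that is a guess which only the authors can confirm.

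**Step 3. Ask whether any of these readings leaves too few completers.**

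- Base 63, true loss 10%: 73 x 0.90 = 65.7 remain, more than 63.
- Base 63, true loss 13.7%: 73 x 63/73 = 63 remain, exactly the base.
- Base 65 or 66, true loss 10%: 65.7 remain, which covers 65 and is within rounding of 66.

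On each reading, enrolling 73 delivers the number that the reading calls for.

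**What cannot be checked.** The 63 itself cannot be reproduced, because the article gives no difference or standard deviation and refers to a cited source instead. The arithmetic above does not depend on it.

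**The case against.** The strongest reply is that this is a clerical slip without consequence. If 63 and 10% are the true inputs, 73 is slightly generous, and step 3 shows that none of the other readings leaves the trial short. That is correct, and it sets the weight of the point. It does not remove it, because the published number still does not follow from the published inputs.

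A reader might infer more than the document supports:

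- **That the 80% power claim is in doubt.** It is not, on these figures. The discrepancy errs towards more participants.
- **That the number of completers needed is unknown.** The sentence names 63 as the number required and 73 as the number after the allowance. Bases of 65 and 66 are only back-calculated candidates and appear nowhere in the article.
- **That the planning effect was a standardised difference of 0.50.** The usual two-mean formula, two-sided at 5% with 80% power, does give 63 for that value. However, the article states neither an effect nor the sidedness, and the source it cites is not available here. The value should not be written into the plan because it happens to fit.
- **That the effect could only have been a standardised one, because the questionnaire did not yet exist.** The article does not say when the calculation was made.
- **That leaving out the difference and standard deviation is a separate fault.** A journal article may leave these to the full protocol, which is not shown.
- **That the trial registration carries the same error.** The registry record is not part of the material reviewed.

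**Conclusion.** The point holds as an arithmetic error in the stated sample size. The figures 63, 10% and 73 cannot all be right. With 63 and 10% the result is 70 per group by either usual convention, so the stated number is 3 per group too high. The document does not show which figure is at fault.

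The size of the problem is modest. The effect on power is nil or slightly favourable if 63 and 10% are right, and validity is not affected. The conclusion rests only on the three stated figures and on reading the 10% as either a proportional addition or a proportion lost. It needs no assumption about the effect size. The point is worth correcting because the recruitment target and the tolerated loss are figures against which the trial's conduct will be judged.

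**What to change.** Correct the sentence under Calculating sample size to whichever of these sets matches the calculation actually made:

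1. 63 per group, and 70 per group (140 in total) after 10% dropout.
2. 63 per group and 73 enrolled per group (146 in total), with the allowance restated as about 13.7% loss.
3. 73 enrolled per group with 10% dropout, and the base corrected to the value actually calculated. A base of 65 (by division) or 66 (by multiplication) would fit.

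The authors should go back to their own calculation to choose, and not pick the set that looks tidiest. The cost is one corrected sentence in the protocol. No extra enrolment is needed, and the design and analysis do not change.

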#### Questionnaire used in this study

The main outcome of the study is promoting of neck pain preventive behaviors that will be assessed using a researcher-made questionnaire. Data collection instrument is a researcher-made questionnaire that is completed and collected in three stages. Therefore, before the intervention, 1 month after the intervention and 3 months after the intervention, the questionnaire is presented to the intervention and control groups for completion. The data obtained in three stages in both groups are analyzed to determine whether the educational intervention is effective in promoting neck pain preventive  behaviors in teachers.

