## Discussion

One of the features of this study is paying attention to promoting health in the workplace. This study will investigate the effect of interventions in promoting preventive behaviors and reducing occupational neck pain among teachers. The main framework of this study will be designing a model-based intervention in social media context to prevent teachers’ neck pain.

The strengths of this study include conducting a qualitative study to design a researcher-made questionnaire, psychometric phase of the questionnaire, designing an educational intervention based on HBM, and implementing the specific intervention using social media and finally compare it with the control group to determine its effects. However, if this intervention is cost-effective, its’ flexibility and accessibility makes it easy for users to access educational content easily. One of the weakness points of the study is the self-report procedures of people about their neck pain perception and behaviors. Another limitation of the study is the lack of time for collecting data on 6- and 12-month follow-ups to determine its continued maintained effects which should be considered in future studies.

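### The protocol article calls the trial double-blind for researcher and participants, but its own description of the two arms makes that impossible, and the main outcome is the unblinded teachers' self-report

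*Protocol article*

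**What the plan says.** Under Calculating sample size, after describing the draw of codes from a bag, the protocol article says: "This study is a double-blind study, so the researcher and participants are not aware of about the grouping of individuals". The sentence names both parties.

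Under Implementation of intervention it describes what each arm gets:

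- Intervention arm: "The intervention group will receive training in the form of webinars, group discussions, questions and answers, videos, animations, posters, pamphlets, and infographics". This runs through social media for 1 month, followed by 3 months of reminder training.
- Control arm: "During this period, the control group will not receive any intervention". Controls are offered the material only later: "the training package will be provided to the control group after the study is finished". The Sampling section also says that controls get no training programme.
- Researcher: "The procedure of teacher training is supervised by the researcher", and "Participants can communicate with the researcher by email and phone call".

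On the outcome, Questionnaire used in this study says: "The main outcome of the study is promoting of neck pain preventive behaviors that will be assessed using a researcher-made questionnaire". Scoring questionnaire has behaviour items answered on a five-point scale from never to always, and says that forms are filled in anonymously. The Discussion lists as a weakness the "self-report procedures of people about their neck pain perception and behaviors".

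**The concern.** The blinding sentence describes a property that the trial, as set out a few sections later, cannot have. A teacher who has sat through a month of webinars and discussions knows it, and so does a teacher who has received nothing. A researcher who supervises the training of one arm knows who belongs to it.

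This matters because of the type of outcome. Teachers rate their own preventive behaviour, so each participant is also the outcome assessor. The training covers posture, ergonomics and neck exercises, which are the kinds of behaviour the questionnaire is meant to capture. Trained teachers may therefore report what they were taught to do, whether or not they do it more often. A between-arm difference could then reflect changed behaviour, changed reporting or both, and the data collected could not separate them. A reader who takes the double-blind label at face value, next to the admitted self-report weakness, could suppose that any misreporting is balanced between arms.

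**Working it through.** **Step 1. The blinding statement against the conduct of the trial.** The point rests on text, and no figure in the plan has to be reproduced.

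| Party said to be unaware | What the article describes | Can the party be unaware? |
|---|---|---|
| Participants, intervention arm | One month of overt, interactive training, then three months of reminders | No |
| Participants, control arm | No intervention until the study ends; no sham or attention control described | No |
| Researcher | Supervises the intervention arm's training; reachable by email and phone | No |

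**Step 2. Who assesses the main outcome.** The instrument is a questionnaire completed by the teacher (Questionnaire used in this study; Scoring questionnaire). The assessor is therefore the participant, who by step 1 is unblinded. The article describes no separate blinded assessor or analyst.

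**Step 3. Illustration of what is at stake.** The documents give no size for reporting bias, so the shift *b* is an assumption and is shown as a range. Inputs:

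- n = 63 per arm, the stated number before dropout allowance (Calculating sample size)
- 5% level, from the stated 95% confidence, taken as two-sided
- two-group t-test (Data monitoring)
- true effect of zero, and a between-arm reporting shift of *b* SD

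Normal approximation: s = b / √(2/n), and rejection rate = 1 − Φ(1.96 − s) + Φ(−1.96 − s). With n = 63, 1/√(2/63) = √31.5 = 5.612.

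| b (SD, assumed) | s | Rejection rate, normal approximation | Rejection rate, noncentral t |
|---|---|---|---|
| 0 | 0 | 0.050 | 0.050 |
| 0.1 | 0.561 | 0.087 | 0.086 |
| 0.2 | 1.122 | 0.202 | 0.200 |
| 0.3 | 1.684 | 0.391 | 0.386 |

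Both methods give about 9%, 20% and 39%. At the stated recruitment target of 73 per arm, the noncentral t rates are 9.2%, 22.5% and 43.7%.

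**The case against.** Several objections have weight.

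- **Blinding is rarely possible in an educational trial with a no-training control.** This is true. The no-training control is not the fault; the fault is a sentence that claims blinding all the same.
- **The sentence may mean only that the draw was hidden.** It stands beside the description of the draw. But concealing the draw is a different property, it ends once training starts, and the sentence calls the study itself double-blind.
- **The article discloses the weakness.** The Discussion does name self-report, and this stands. It does not connect self-report with teachers knowing their arm.
- **Questionnaires are anonymous.** This may weaken the wish to please the researcher and deserves credit. It does not hide a teacher's own allocation from that teacher.
- **The rejection rates do not measure the error.** This stands. They rest on assumed shifts and would be the same in a trial openly described as unblinded. Deleting the sentence changes none of them.
- **An attentive reader will see that controls get no training.** The article says so plainly, so how many readers would be misled is unknown.

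A reader might also infer more than the text supports. The article nowhere claims that blinding protects the self-reported outcome; that would be read into the label. Nothing suggests that forms or invitations differ between arms, since the questionnaire goes to both groups at the same three time points. The registry entry is not shown, so nothing can be said about how it describes blinding.

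**Conclusion.** The double-blind statement is false as written. It is contradicted by the Sampling and Implementation of intervention sections, and no detail in a fuller protocol or analysis plan could make it true while those sections stand. It must be corrected, because it misstates a core design property that bears on how the main outcome can be read: the outcome is rated by people who know their allocation.

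The size of any resulting bias is unknown. Shifts of 0.1 to 0.3 SD would raise the false-positive rate from 5% to about 9% to 39%, assuming no true effect, 63 per arm and a two-sided 5% test. This shows the sensitivity of an unblinded self-reported comparison. It is not evidence that such a shift will occur, nor a measure of harm from the label. A reader might conclude that the comparison is invalid or that the control arm must be redesigned; the documents support neither. The correction concerns what the trial says about itself and what it may conclude.

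**What to change.** 1. Withdraw the double-blind sentence under Calculating sample size.
2. State that participants and the researcher who supervises the training are not blinded.
3. Limit any blinding claim to what can be done, for example arms coded A and B in the dataset until the primary analysis is final. Claim this only if it will be done.
4. In the Discussion, link the self-report limitation to the lack of blinding. Anonymous completion may be mentioned as a partial safeguard, with the remark that it does not conceal a teacher's own allocation.
5. Word conclusions as effects on self-reported preventive behaviour.

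The cost is a few sentences and a coded arm variable. Sample size, intervention, questionnaire and tests do not change. The downside is a less favourable design label.
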